## **6.2.Strategies for addressing recruitment / assessments if Covid-19 lockdown restrictions are in place:**

During Covid-19 social restrictions, a researcher verified weight assessment using a standardised method (see Section 6.6 for more details) is essential for participants to enrol in Game of Stones. Obtaining verified weights is crucial for incentive trial validity and would not be possible to undertake via a live video assessment, unless with appropriate Personal Protective Equipment (PPE). Assessments may be acceptable outdoors or in GP practice or community venues e.g. pharmacy shops, charities, local authority services who are in agreement. All other trial assessments could feasibly be undertaken using video assessments. In the event of a full Covid-19 lockdown, where face-to face verified weight assessments cannot take place, recruitment would continue, with men placed on a waiting list for enrolment once Covid-19 restrictions allow weight verification.

Recruitment: approach by letter via GP register, social media, community stakeholders (e.g. link workers, community workers), posters and newspaper adverts (the flier/poster) can continue remotely. Community recruitment approaches will be modified to ensure full compliance with current local Covid-19 restrictions which are likely to involve: situating stands outside venues, maintaining physical distancing from potential participants, use of antibacterial hand sanitiser gel/wipes and both participant (if appropriate) and Fieldworkers wearing PPE e.g. face coverings. Those interested in participating will be asked to leave their contact details either by scanning a QR code to enter details on their smartphone or by the Fieldworker noting contact details/preferred method of contact. Interested men will also be directed to the study website for further information with the web page and team contact details available in a format that is easy for them to photograph with a mobile phone. Due to potential involvement of GP practices in a Covid-19 vaccination programme, it may be necessary to increase recruitment via the community approach to avoid putting additional strain on GP practices. If vaccination is being undertaken in community venues (halls, sports centres), then researchers would request permission to have information stands. If recruitment numbers are affected by Covid-19, the research team will approach The Scottish Health Research Register (SHARE) to request access to their database of potentially eligible adults who are willing to participate in research.

Enrolment: first contact made by the Fieldworker will be made remotely using the potential participant's preferred method of contact e.g. mobile phone, landline, email, Facetime, Zoom, Microsoft Teams or Skype during which the trial will be explained further. Should individuals wish to proceed in the trial a postal address will be taken to which a participant consent form, Full PIL and baseline questionnaires will be sent electronically (paper back-up). A second appointment (preferred contact) with the Fieldworker will be made to complete the consent and baseline paperwork. The participant will be asked to initial, sign and date the consent form during the discussion. This is called "verbal confirmation of

written consent” and this will be documented by the Fieldworker. The participant will then be asked to either return the consent form by post or to bring the consent form with them to their baseline weigh-in appointment. When the consent form is returned, the member of the local site research team with delegated responsibility for consent and who conducted the consent discussion over the phone will countersign and date the consent form. The date of countersignature should not be earlier than the date of the participant signature but may be later. Randomisation can only be triggered by confirming eligibility at the baseline weigh-in appointment. Fieldworkers should not proceed with obtaining baseline weight measurement if a hard copy of the consent form has not been received in the post or given to the Fieldworker on the day of the appointment. Where verbal confirmation of written consent is not followed by receipt of a hard copy of the written consent form, the participant will not be randomised or progress further in the trial.

**Baseline weigh-in: Face-to-Face baseline weigh-in** (this must be conducted face-to-face, no remote option permissible) will be modified to ensure full compliance with current local Covid-19 restrictions. On the day prior to the appointment, participant and Fieldworkers will confirm that neither has any symptoms or have been in contact with Covid-19, in accordance with Government guidance (see Section 6). The weigh-in appointment is likely to involve: meeting participants outside where possible (whilst ensuring sufficient privacy), maintaining physical distancing, use of antibacterial hand sanitiser gel/wipes and both participant (if appropriate) and Fieldworker wearing PPE e.g. face coverings. The fieldworker will supply all equipment needed to comply with current guidance for both themselves and the participant. Participants will be asked to meet the Fieldworker somewhere that they feel comfortable attending, which may include their own home. If attending a participant’s home, Fieldworkers should seek to conduct the weigh-in appointment in a private space outdoors where possible or in the entrance to a person’s home in order to avoid contact with surfaces. Post-randomisation a wallet-sized Game of Stones appointment card and post-randomisation leaflets will be given to the men (post/email options). All equipment with hard surfaces will be wiped down before and after contact with participants with sanitising wipes.

**Follow-up appointments:** will be offered as above, in accordance with changing government guidance on Covid-19 restrictions. 3, 6 and 24M weigh-in appointments have a target time of around 10 minutes. The weighing will take place first and then questions about adverse events (see Section 8). At 3 and 6M appointments the SWAT protocol will guide how fieldworkers deliver the weigh-in. If face to face assessment is inadvisable or unacceptable, remote video assessment will be arranged. Short term provision of weighing scales for the assessment may be required. The 12M appointment would normally last 30 minutes (video option if in person assessment not possible). However, the face to face component could be reduced to a 10-minute weigh-in following the same protocol as the 3, 6, and 24M assessments or conducted by video. If face to face assessment is not possible, all assessments can be

done by video, apart from weight at baseline. Participant self-report questionnaires could be completed on-line, by post or by telephone with a researcher (if visual or literacy concerns). All options would be available for the 12M assessment if circumstances warranted this. Methods of data collection will be clearly documented for each assessment.

### **6.3. The randomisation scheme**

After receiving written consent, the Fieldworker will randomise men using a secure remote web-based system provided by the CHaRT CTU, with telephone randomisation available as a backup in case of internet problems. The CHaRT randomisation service is independent of the data management and statistical team at CHaRT who will be undertaking the outcome data analysis. Randomisation will be stratified by trial centre using random permuted blocks. Participants and the Fieldworker are informed automatically by SMS about group allocation. At the same appointment, the Fieldworker then provides additional verbal and written information appropriate to the allocated group, and a unique website login and password that allows access to the web pages for that trial group. Where this takes place will be negotiated according to the local Covid-19 restrictions and participant preference. HIC recruitment tracker is linked to the group allocation to facilitate the delivery of the automated SMS and Incentive interventions. Separating the institutions involved in intervention delivery (HIC) from the randomisation service and outcome data analysis facilitates blinding of the statistical team.

Due to the low-risk and self-management nature of this public health trial, the participant's GP will not be informed of their participation in this trial.

### **6.4. Blinding**

Primary outcome assessment will be blinded to group allocation and undertaken by a Fieldworker who has not previously met the man and/or is not aware of study group. This was tested in our Feasibility Study and found to be acceptable, understandable to participants and feasible logistically for Fieldworkers to implement. When assessments are arranged, participants will be asked not to inform the Fieldworker conducting follow-up appointments of their group allocation. Recruiting GP practices or other stakeholders who facilitate recruitment (e.g. community centre staff) will not be informed of group allocation. The statistical team analysing data will be blinded to group allocation and will not have access to data collected at 3M and 6M outcome assessments in the intervention groups during the primary analysis.

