### ***Trial Coordinating Team***

The trial will be coordinated by the CI and Trial Managers based at NMAHP RU at Stirling University. The Trial Managers will be responsible for the day to day transaction of trial activities (supported by [name], senior trial manager at CHaRT) and coordinating work conducted by the Fieldworkers at each of the 3 centres via their Centre Leads. The Fieldworkers are responsible for day to day recruitment and follow up of participants; data collection and management; liaising with PPI and Stakeholders and assisting the process evaluation team. Two Fieldworkers at each centre will be supported by a pool of postgraduate students, so that recruitment can occur flexibly at weekends and in the evenings, enabling men who work to join the study. This was effective and efficient in the Feasibility Study.

A trial-specific delegation log will be prepared for each centre, detailing the responsibilities of each member of staff working on the trial.

The CI, Trial Managers and Qualitative Research Fellow will meet weekly, with others invited when required. The CI, Trial Managers and Centre Leads will meet fortnightly/monthly (depending on stage of trial), with others invited when required.

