## 5. TRIAL DESIGN

A pragmatic, multi-centre, parallel, 3-arm, assessor blind, RCT comparing weight change at 12M for: i) SMS with endowment incentive; ii) SMS only and iii) 12-month waiting list control for SMS delivered M13-15 inclusive), with 24M follow-up (i.e. 1 year post intervention), mixed methods process evaluation including qualitative interviews (participants and commissioners), cost-effectiveness modelling and consent for future data linkage to longer term health outcomes. There are three phases: 1. Trial set-up and integrating scalability; 2. RCT; 3. Long-term cost effectiveness, scalability and follow-up.

A secure CTU web-based system will be used to randomise men, stratified by recruitment centre.

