## 8.8. Safeguarding

In the text message intervention groups, men may reply to the text messages being delivered. The Health Informatics Centre in Dundee have experience of automatically screening incoming text messages from participants in similar studies[31-33] for words like 'suicide', 'die', 'death', 'help'. The trial will use this screening process.

In the intervention groups, if a text message from a participant contains a keyword (e.g. help, suicide, death, die) the message is given high importance. Monitoring will run for the duration of the trial assessment period (24M). The HIC monitoring service will send the message in an email to appropriate researchers (the site Fieldworkers and the Trial Managers), providing the participant ID number and content of the text message.

If the research team is concerned regarding the content of a message, they will discuss this with a senior colleague (CI or medically qualified delegate). Similarly, if any issues are raised during any contact with a participant that cause concern (for example if a participant tells a Fieldworker that he feels suicidal), this will be discussed with the PI, and then CI or medically qualified delegate. In these circumstances, the allocation can be unblinded if necessary, and a course of action will be agreed. If the safety of the participant or of another person was thought to be at risk, a member of the research team will alert appropriate services: informed consent is sought for this when men join the study.

Patient information leaflets and information available on the GoS website will provide local and national contacts where men can access support.

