#### **11.6. Data protection and patient confidentiality**

Patient confidentiality will be maintained for all collected data. All investigators and trial site staff will comply with the requirements of the General Data Protection Regulation (GDPR) (or subsequent legislation), with regards to the collection, storage, processing and disclosure of personal information and will uphold the Act's core principles.

Computers used to collate the data, and the trial website will have limited access measures via usernames and passwords. Staff at sites only have access to participant data for participants at their site. Within the study website, identifiable data is stored with a strong encryption algorithm (currently the key used is AES\_256). Participants will be identified using a unique participant ID number.

Participant data, contact information and responses to text messages will be managed electronically in the Participant Tracker Software at the Health Informatics Centre, University of Dundee which is an approved NHS safe haven for data. Data handling and storage will comply with GDPR legislation. Researchers employed by the three trial centres (Universities of Stirling, Bristol and Queens Belfast) will have secure passwords to access the Participant Tracker system at the University of Dundee.

Data from qualitative interviews will be anonymised by removing any information which could potentially identify the participant. Only interview transcribers who are approved by the University of Stirling and

meet confidential data handling requirements will be used. Each participant will have a unique participant ID number. The interview recordings, transcriptions and NVivo database will be password protected and encrypted and stored securely at the University of Stirling. The recorder will be wiped clean as soon as the recording has been stored. Personal data and audio recordings will be destroyed as soon as it is certain that they are no longer required (i.e. at the end of the study/follow-up period).

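### The wording of the 12-month blinding rule does not consistently require the assessor to be unaware of the group, and the stated safeguard leaves two routes to awareness uncovered

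*Protocol*

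**What the plan says.** Section 5 declares "A pragmatic, multi-centre, parallel, 3-arm, assessor blind, RCT comparing weight change at 12M". Section 6.4 carries this into an operating rule: the assessment of the primary outcome is to be blinded to allocation and "undertaken by a Fieldworker who has not previously met the man and/or is not aware of study group". Men are asked not to reveal their group, in section 6.1 (future appointment preferences) and again in section 6.4, which adds that the arrangement was tested and found workable in the Feasibility Study.

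Other sections bear on what a Fieldworker may know:

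- Section 8.8: when a text from an intervention participant contains a keyword, the monitoring service will "send the message in an email to appropriate researchers (the site Fieldworkers and the Trial Managers", giving the participant ID and the message.
- Section 11.6: "Participant data, contact information and responses to text messages will be managed electronically in the Participant Tracker Software", and researchers at the three centres hold passwords to it.
- Section 6.3: "HIC recruitment tracker is linked to the group allocation to facilitate the delivery of the automated SMS and Incentive interventions".
- Section 2.1 (Trial Coordinating Team): "Two Fieldworkers at each centre will be supported by a pool of postgraduate students".
- Sections 6.6, 7.4 and 9.11: questionnaires are completed with the researcher present, who checks them for gaps. The 12-month questionnaire has items on engagement with the interventions, and SWAT participants also complete the CARE measure at 12 months.
- Section 6.2 (follow-up appointments): weighing before questions follows the sentence on the 3, 6 and 24-month visits. At 12 months it applies expressly only if the visit is shortened to a weigh-in.

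**The concern.** The 12-month weight is the primary outcome and, in the SMS+I arm, it also determines the payment (section 7.3.2). The reading comes from calibrated scales, but the Fieldworker still has some discretion over how firmly to apply the instructions on clothing and pocket contents (section 6.6). Blinding is meant to keep knowledge of the arm out of that discretion.

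Centres will roster staff from the descriptive half of the sentence in section 6.4. If either condition is enough, a centre can follow that half and still send someone who knows the arm. The protocol provides no record of assessor awareness, so this could be neither detected nor examined afterwards, and the trial would be reported as assessor blind.

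**Working it through.** **The rule.** There are four possible states of a 12-month assessor:

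| Met the man? | Knows his group? | Opening clause of 6.4 and section 5 | Descriptive clause of 6.4, read literally |
|---|---|---|---|
| No | No | Acceptable | Acceptable |
| Yes | No | Acceptable | Acceptable |
| No | Yes | Not acceptable | Acceptable |
| Yes | Yes | Not acceptable | Not acceptable |

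The two halves disagree in the third row only. The question is then whether the protocol lets someone who has not met a man learn his group.

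**Routes.**

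1. *Keyword emails (8.8).* These go to the site Fieldworkers with the participant ID. Controls receive no SMS until month 13 (7.2), so an email before the 12-month visit shows that the man is not a control. It need not separate SMS from SMS+I. Both primary contrasts are against control (9.3.2), so partial unblinding still matters.
2. *12-month questionnaires (6.6, 7.4, 9.11).* Engagement items and the CARE measure can indicate an intervention arm to the researcher who checks the form. This is harmless if the weight is already recorded, but that order is not clearly stated for the standard 12-month visit (6.2).
3. *Tracker (6.3, 11.6).* It is linked to allocation and centre researchers have passwords. Whether Fieldworkers can see allocation or all text replies in it is not stated, so it is not counted here as a documented route.

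Asking men not to disclose covers neither route 1 nor route 2.

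**Size.** The inputs from section 9.1 are a difference of 3.3 kg, SD 8 kg, two-sided alpha 2.5%, 90% power, 146 followed up per group, 25% loss and a mean baseline weight of 109 kg.

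The plan's own figures reproduce:

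- n = 2 × [8 × (2.2414 + 1.2816) / 3.3]² = 145.88, so 146 per group.
- 146 / 0.75 = 194.7, so 195 per group, and 3 × 195 = 585.

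Standard error of one contrast: 8 × √(2/146) = 0.94 kg.

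No document gives the frequency or size of any mis-weighing, so both are assumed. If a fraction f of intervention weights is recorded b kg too low, the contrast shifts by f × b:

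| f | b (kg) | Shift (kg) | Percentage points at 109 kg | Rejection rate with no true effect |
|---|---|---|---|---|
| 0.10 | 0.2 | 0.02 | 0.02 | 2.5% |
| 0.25 | 0.5 | 0.125 | 0.11 | 2.6% |
| 0.50 | 0.5 | 0.25 | 0.23 | 3.0% |
| 0.50 | 1.0 | 0.50 | 0.46 | 4.7% |

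An average shift of 0.5-1.0 kg across the whole arm would be 15-30% of the target (0.5/3.3 and 1.0/3.3), or about 0.5 to 1.1 standard errors. That is an upper case, because it amounts to every intervention weight being affected by that much.

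**The case against.** The strongest reply is that the sentence in section 6.4 starts by requiring blinding. A knowing assessor breaches that clause and section 5, whatever follows. A reader might infer that the protocol permits a knowing assessor and counts him as blinded. It does not say so; that is one literal reading of inconsistent wording.

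A reader might also infer that Fieldworkers see allocation and every text reply in the tracker, and so that unblinding is likely. The documents do not support this. The allocation link is described as serving delivery, only keyword-flagged messages are documented as reaching Fieldworkers, and nothing indicates how often that would happen.

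Further points stand in the plan's favour. Men are asked not to disclose, the arrangement worked in the Feasibility Study, the scales are calibrated and the man signs the entry. The student pool makes it easier to find an assessor who has not met the man. The weighing-first sentence sits under a general follow-up heading and does not expressly exclude 12 months.

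These points limit the concern without removing it. The two halves of the rule still conflict, the keyword emails are explicit, the order at the standard 12-month visit is unclear, and the non-disclosure request covers neither route.

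**Conclusion.** The point holds as an inconsistency to be corrected, with a modest and unquantified risk to the primary outcome. Section 6.4 requires blinding and then describes the assessor in terms that, taken literally, do not require unawareness. Two documented routes could tell an assessor that a man is not a control.

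The illustrated shift of 0.02-0.50 kg depends wholly on assumed values: 10-50% of intervention weights affected, by 0.2-1.0 kg, all in one direction. It also uses the planning SD of 8 kg and 146 men per group, and is converted from kg although the primary outcome is percentage change. At its top end, the rejection rate with no true effect rises from 2.5% to 4.7% per comparison. The figures are no evidence that such bias will occur. An average shift of 0.5-1.0 kg should not be taken as the expected size, and nothing here alters the sample size.

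**What to change.** 1. In section 6.4, require every 12-month assessor to be unaware of the man's group. Keep not having met him after randomisation as an added preference, not an alternative.
2. State that any Fieldworker who has learned a man's allocation, including through a safeguarding email, does not take his 12-month weight. Leave the alert pathway in section 8.8 unchanged, since it serves participant safety.
3. State in sections 6.2 and 6.6 that at 12 months the weight is taken, entered and signed before any questionnaire or adverse-event question.
4. Add one CRF item on whether the assessor knew the group, so that a sensitivity analysis is possible. The analysis itself can be specified in the SAP.

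The cost is a few sentences of protocol text, one extra CRF item and slightly less flexible rostering. The existing Fieldworkers and student pool should be able to cover the exclusions.

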## **6.5. Baseline data**

Demographics and measures collected at baseline are summarised in Table 1 and are based on the FFIT trial [16] and the recently published STAR-LITE core outcome set for behavioural weight management interventions [17].

## **6.6. Trial assessments**

The methods of data collection adhere to the same protocol that was shown to be acceptable and feasible in our Feasibility Study [1, 2]. Potential modifications for various Covid-19 restrictions and scenarios are described in Section 6.2 and the schedule of assessments is summarised in Table 1. Participants will be sent a reminder of their appointment by text (or preferred contact method) the day before. Non-attenders will receive two reminders to contact the team and given the opportunity to arrange another appointment. Reminders will use different methods e.g. SMS, email, phone, post because mobile phone numbers may change, harder to reach men may run out of phone credit and some men unpredictably work away from home (zero hours contracts). Flexibility of approach is both valued by participants and required in any study aiming to address health inequalities. Relevant information about preferred methods of contact is documented by fieldworkers on recruitment tracker. In the feasibility study, some men wished to attend assessments and stay in the study but decided to stop receiving the texts. Fieldworkers will use a portable stadiometer (height) and calibrated scales (weight). Weight will be entered manually onto the Case Report Form and participants will be asked to sign to agree the weight entered. Fieldworkers will measure weight using standardised procedures and following device instruction manuals within a 3-week window of their personal weight target date in order to qualify for the linked incentive at 3, 6 and 12M. Men are requested to take off shoes, remove bulky clothing and empty pockets. Hard copies of all participant anthropometric measurements will also be noted to prevent any missing data caused by technology failure.

In the event of a face-to-face verified assessment not being possible for the primary outcome assessment at 12M (e.g. participant out of the country), every effort will be made to gain a satisfactory verified weight via video assessment, or via an independently confirmed weight by third party e.g. a pharmacist, community or health worker. Methods will be documented, to enable a sensitivity analysis to be undertaken (see Section 9.9). Besides Covid-19 restrictions, two additional scenarios where this would apply were encountered in the Feasibility Study: unexpectedly working abroad; admitted to hospital.

Self-report questionnaires (participant choice, online, paper, telephone if visual impairment or literacy issues - method documented), completed when attending weight assessments, will be uploaded to CTU databases. The questionnaires are completed by the men with the researcher present in case they require help e.g. visual or literacy issues. When completed, the researcher will check to make sure there

is no accidental missing data (e.g. two pages turned over). If missing data is noticed after the assessment appointment, the participant will be phoned as soon as possible and given an opportunity to provide the missing data. Any missing data completed after the assessment will be logged. Assessments use validated tools where available and follow quality standards for measurement procedures.

To maximise completeness of data, participants who do not attend assessments within the 3-week time window permitted, but who have not withdrawn from the trial, may be contacted (by their preferred method) and requested to complete a questionnaire (preferred method) and provide a self-report weight. This will not qualify for an incentive payment. A letter will be sent to those who don't attend the 12M assessment reminding them that they will be invited to attend an appointment at 24M.

All participants receive a £20 voucher (Amazon or High Street) reimbursement of expenses for attending the 12 and 24M assessments, consistent with evidence that financial reimbursement can improve retention [36, 37]. In the Feasibility Study data quality was high, with low levels of missing data. The completion rates for self-reported secondary outcomes were 88-99%. The Delegation of Responsibilities Log will identify all trial personnel responsible for data collection, entry, handling and managing the database.

